### Sample size

The primary outcome is change from baseline to 12 months in average daily physical activity as quantified by ENMO and measured in milligravitional units (m*g*). In order to detect a minimum clinically significant difference of 2.1 m*g*, which is equivalent to an overall increase in physical activity volume of approximately 10 metabolic equivalent hours per week and is consistent with minimum recommendations for health, and assuming a standard deviation of 5.3 m*g* [60], a power of 80% and a significance level of 5%, the sample size requires 202 participants. To allow for 20% loss to follow-up and 20% non-compliance of accelerometer/intervention attendance, we will need to recruit 338 participants (169 in each arm).

### Statistical analysis

A Consolidated Standards of Reporting Trials (CONSORT) diagram will summarise the flow of participants through the study. Descriptive characteristics at baseline will be summarised by arm. Numbers (with percentages) for binary and categorical variables, and means (and standard deviations) or medians (with lower and upper quartiles) as appropriate for continuous variables will be presented. Preliminary graphical and tabular presentations of the data will be inspected for the correct statistical modelling assumptions.

The primary analyses will use a complete case population (i.e. participants with a complete log and valid outcome measurements). For the primary outcome (change in average daily physical activity), the intervention group will be compared to the control using a linear regression model with a binary indicator for randomisation group as the explanatory variable; terms for the stratification factors (ethnicity and gender) as confounders; and adjustment for the change from baseline in accelerometer wear time and baseline average daily physical activity. Sensitivity analyses will include a per-protocol analysis and an intention-to-treat analysis where missing data will be imputed using multiple imputation or another suitable method. Sensitivity analysis will also test whether outcomes are robust if physical activity data are restricted to those with at least 3 days of valid data. Interaction effects will be fitted between intervention arm and gender (male vs. female), and ethnicity (White European vs. other). If the interaction term is statistically significant (at the 10% level), then stratified analyses will be performed for that factor using the same model as the primary analyses. Secondary outcomes will be analysed using similar methods as in the main analysis, with an appropriate model selected dependent on the distribution of the outcome. A detailed statistical analysis plan will be written and approved before the database is locked.

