### Primary outcome

The primary outcome measure is change in objectively measured physical activity from baseline to 12 months using the GENEActiv wrist-worn triaxial accelerometer (GENEActiv model 1.1, ActivInsights Ltd., Cambridgeshire, UK) with a dynamic range of +/− 8 *g*, where *g* is equal to the Earth’s gravitational pull. Participants are asked to wear the GENEActiv accelerometer on their non-dominant wrist for 8 consecutive days (24 h), wearing the monitor from the date of the assessment visit or from a specified date when sent in the 6 months postal follow-up. The accelerometer is initialised to collect data at 100 Hz. An appropriately trained individual instructs the participant on correct placement of the monitor. Participants are asked to complete a log whilst wearing the monitor to provide their waking hours and wear time information. Participants are given a stamped addressed envelope in which to return the monitor and log sheet once completed. Accelerometer data will be calibrated and analysed according to best practice procedures through the Lifestyle Theme of the National Institute for Health Research (NIHR) Leicester Biomedical Research Centre. In brief, data will be processed and calibrated using a bespoke open source package in R (GGIR, http://cran.r-project.org) [46, 47] according to criteria previously described [48]. Data will be included if participants have one or more valid days of data, with a valid day defined as at least 16 h of wear time. The primary outcome is defined a priori as average movement intensity as quantified by the Euclidean norm minus 1 *g* (ENMO) method. In addition, time asleep, sleep quality and time in sedentary behaviour; light-intensity physical activity; and moderate to vigorous physical activity will also be derived using validated algorithms and thresholds.

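### The primary analysis population requires a complete wear log on top of a valid accelerometer outcome, an undefined extra condition that excludes randomised participants with usable primary data

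*Protocol article*

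**What the plan says.** The Primary outcome section of the protocol article sets out the measurement. Participants are asked to "wear the GENEActiv accelerometer on their non-dominant wrist for 8 consecutive days (24 h"). The outcome is then fixed: "The primary outcome is defined a priori as average movement intensity as quantified by the Euclidean norm minus 1" *g* (ENMO), obtained by processing and calibrating the accelerometer data in an R package. The validity rule is "Data will be included if participants have one or more valid days of data". The threshold for such a day follows in the same sentence: "with a valid day defined as at least 16 h of wear time". No log condition is attached to it.

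The same section describes the log: "Participants are asked to complete a log whilst wearing the monitor to provide their waking hours and wear time information". Participants receive "a stamped addressed envelope in which to return the monitor and log sheet once completed".

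The Statistical analysis section then defines who is analysed: "The primary analyses will use a complete case population (i.e. participants with a complete log and valid outcome measurements"). The primary model includes "adjustment for the change from baseline in accelerometer wear time and baseline average daily physical activity". Three sensitivity analyses are listed: per protocol, intention to treat with missing data imputed, and a restriction to participants with at least 3 valid days. A detailed statistical analysis plan is to be approved before database lock.

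**The concern.** The log is joined by 'and' to an outcome that is already valid, so it can only remove people. Someone with valid ENMO at baseline and at 12 months but gaps in the log meets the device rule and is still left out of the primary comparison.

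Two things are at stake.

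- **Lost information.** Valid measurements of the primary outcome are set aside, and the article states no gain in outcome validity in return.
- **Selection after randomisation.** The 12-month log is filled in after randomisation by participants who know their arm (Randomisation and blinding). The intervention makes self-monitoring a key part of the programme and issues pedometers (Intervention group), so log completion could plausibly differ between arms. Conditioning the primary comparison on it weakens the protection that randomisation gives.

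The word 'complete' is also open. It could mean all eight days or only some, and one visit or both. Until it is defined, the primary population is not fully specified.

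**Working it through.** **Step 1: who each rule admits**

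| Participant | Device validity rule (Primary outcome) | Primary population (Statistical analysis) |
|---|---|---|
| Valid ENMO at both visits, log complete | usable | included |
| Valid ENMO at both visits, log incomplete | usable | excluded |
| No valid day at 12 months | not usable | excluded |

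The second row is the whole of the problem. The two rules are nested: the analysis population is the device rule plus one more condition.

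**Step 2: what the log could be needed for**

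ENMO is processed from the accelerometer data. The log supplies waking hours and wear-time information. Wear time enters the primary analysis twice, in the 16 h valid-day rule and as the change-in-wear-time covariate. The article calls the covariate accelerometer wear time but does not say whether it is derived from the device signal or from the log. Even if the log is its source, one valid day would need log information for that day, not a complete log of an 8-day period.

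**Step 3: whether a listed sensitivity analysis covers it**

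The 3-day restriction changes the number of valid days and leaves the log condition alone. The intention-to-treat analysis imputes missing data, but the article does not say whether a participant with an incomplete log keeps the observed ENMO or has it imputed. As written, no listed analysis isolates the effect of the log condition.

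**Step 4: the plan's sample size, reproduced**

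Inputs from the Sample size section: difference 2.1 m*g*, SD 5.3 m*g*, power 80%, significance level 5% (two-sided assumed, since sidedness is not stated), and allowances of 20% and 20%.

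- Normal approximation: n per arm = 2 × (1.96 + 0.84)² × (5.3/2.1)² ≈ 100, or 200 in total.
- Two-sample t calculation: 100.96, so 101 per arm, or **202** in total. This matches.
- Inflation with the allowances summed: 202 / (1 − 0.40) = 336.7, raised to **338** for equal arms. This matches.
- Back-check: 338 × 0.60 = 202.8, so there is almost no reserve above 202 if the whole 40% is lost.

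**Step 5: illustration of further loss through the log**

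The article gives no rate of log incompleteness, so the rates q below are assumed. Power is that of a two-sample t-test with m = 101 × (1 − q) per arm and non-centrality (2.1/5.3) × √(m/2).

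| Assumed q | Analysed n = 202 × (1 − q) | Power |
|---|---|---|
| 5% | 192 | 78.0% |
| 10% | 182 | 75.7% |
| 20% | 162 | 70.7% |

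If a complete log is required at both baseline and 12 months, modest losses at each visit compound. Assuming independence, 95% completeness per visit gives 0.95² = 90% with both logs, and 90% gives 0.90² = 81%.

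**Step 6: the same illustration from the other end**

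The second 20% allowance covers accelerometer and attendance non-compliance together, and the primary analysis does not exclude people for poor attendance. If that whole 20% were non-attendance, 338 × 0.80 = 270 would be analysable. A 20% log loss would then leave 270.4 × 0.80 = 216, with nominal power of about 83%. That figure uses the undiluted 2.1 m*g*, as Step 5 does; non-attendance would itself dilute the effect.

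**The case against.** The strongest reply has four parts.

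1. **The sections do not contradict each other.** One says when accelerometer data count as valid; the other says who is analysed, and its reference to valid outcomes takes in the first. This stands. A reader might infer that the article gives two rival primary populations, but it gives one, with an added condition. The criticism is of that condition.

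2. **The log may have a purpose in the primary analysis.** A complete-case population normally requires the model's covariates, and wear time is one of them. This stands in part. A reader might infer that the log is irrelevant to the primary analysis, and the article does not support that: it ties the log to wear time, never states where the covariate comes from, and refers to processing criteria in a source not available here. But this purpose would justify log information for the valid days used, not a complete log.

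3. **The detail belongs in the analysis plan, and the loss may be small.** The meaning of 'complete' can properly be settled there. If it means little more than a sheet returned with times for the valid days, few people would be excluded. What cannot be deferred is that the protocol has already named the log as a condition of the primary population.

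4. **The loss may already be budgeted, and bias is conjecture.** The log is part of the accelerometer procedure, so the existing allowance may cover it, although logs are not named. A reader might infer from Step 5 that the trial will be underpowered. Step 6 shows why that does not follow. Likewise, nothing in the article shows that log completion differs by arm; it shows only that it could.

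**Conclusion.** The point holds as a badly chosen condition on the primary population. The rule as written excludes randomised participants with a valid primary outcome because of an undefined, self-completed record that, at 12 months, is made after randomisation by unblinded participants. The article states no benefit that would offset this.

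Its size is unknown. The number excluded and the direction or amount of any bias cannot be derived from the document. Power of about 78%, 76% or 71% follows only if 5%, 10% or 20% of 202 evaluable participants are lost for this reason, on a two-sided 5% test. With about 270 analysable, a 20% log loss would still leave about 83% nominal power. The stated 202 and 338 are reproduced and are not in error.

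The correction is worth making because it concerns the confirmatory comparison and costs almost nothing. The article reports recruitment as ongoing and the analysis plan as still to be written, so it can be settled before database lock.

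**What to change.** - **Primary population:** all randomised participants with valid accelerometer data, as defined in the Primary outcome section, at both baseline and 12 months, regardless of log completeness.
- **Wear time:** state its source. Take wear time for the 16 h rule and for the change-in-wear-time covariate from the accelerometer data. If the log is in fact the source, require log entries only for the valid days used.
- **Complete-log restriction:** define 'complete', then use the restriction as a sensitivity analysis and for secondary variables that depend on the log.

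The cost is a change of wording in the protocol and analysis plan and one added sensitivity analysis. The sample size of 338 is unaffected.

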### Randomisation and blinding

Study identification numbers are assigned sequentially, and participants are individually randomised (1:1) stratified by gender (men; women) and ethnicity (White European; other) using a variable block size after their baseline assessment. In order to prevent contamination, an exception is made for individuals from the same household who are allocated to the same group. The randomisation schedule was developed by an independent statistician, and allocation of randomisation is carried out by a researcher independent of the team. Randomisation dictates whether the participant receives standard care or is invited to attend the Movement through Active Personalised engagement (MAP) programme.

After randomisation both groups are sent a letter informing them of the outcome of the randomisation; in addition, intervention participants are contacted by telephone to discuss the dates available for them to attend the intervention. They are then sent a letter confirming the venue, dates and times of the programme. Since the intervention is a group self-management programme, participants and the central study team cannot be blinded to the randomisation. The research nurses who run the follow-up clinics are not informed of the randomisation of the participants attending, and staff analysing accelerometer data to derive the primary outcome are blinded.

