#### Intervention group

Those randomised to the intervention group are invited to attend the MAP programme. The programme comprises four facilitated group sessions delivered in local community settings. The sessions are run approximately 2 weeks apart and last about 1.5 h. The first session takes place within approximately 1 month of consent.

The MAP programme was developed using an iterative process, including a literature review to identify effective strategies within this population, and co-production with patient and public involvement (PPI) and other stakeholder groups (including clinicians and nurses who work in primary care). The literature review guided a content focus on the key generic challenges for this patient group: mastering emotions, managing treatments and communicating with a range of carers (family and health care professionals). The group discussions informed the content and format of the programme to include both a focus on increasing physical activity as well as the generic self-management challenges. The design of the programme was theoretically informed by social learning theory [35] and focussed carefully on the role of the facilitator to support participants to explore their own beliefs, understanding and concerns related to living with two or more long-term conditions. The design of the programme was underpinned by a fundamental belief that individuals know what is best for their health, yet may be more informed in their decision-making by taking part in an open and honest discussion that focusses on increased knowledge and insight through shared experiences [36].

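### The programme is delivered in groups in one arm only, and households share an allocation, but the sample size and the stated primary regression treat every participant as independent

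*Protocol article*

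**What the plan says.** Under Intervention group, the Protocol article says: "The programme comprises four facilitated group sessions delivered in local community settings". The same section makes discussion among participants the main format, led by a trained facilitator. Under Control group, participants stay with routine care and belong to no group.

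Under Randomisation and blinding, allocation is individual ("participants are individually randomised (1:1) stratified by gender (men; women) and ethnicity (White European; other"), except that people from one household go to the same arm.

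Under Sample size, the inputs are a "minimum clinically significant difference of 2.1" mg, "assuming a standard deviation of 5.3" mg, and "a power of 80% and a significance level of 5%, the sample size requires 202 participants". The only inflation is this: "To allow for 20% loss to follow-up and 20% non-compliance of accelerometer/intervention attendance". No course size, ICC or design effect appears.

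Under Statistical analysis, the intervention group is "compared to the control using a linear regression model with a binary indicator for randomisation group as the explanatory variable". The model adjusts for gender, ethnicity, change in wear time and baseline activity. Secondary outcomes follow similar methods.

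**The concern.** The design is partially nested: one arm is grouped after randomisation and the other is not. People on the same course share a facilitator, a venue and the discussion itself. The article treats peer exchange as part of how the programme works. It also plans to observe facilitators for fidelity, which accepts that delivery may vary. If that variation reaches physical activity, outcomes within a course are correlated. The intervention-arm mean then carries more variance than a regression with independent errors assumes.

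The standard error of the treatment effect would be too small, its confidence interval too narrow and the planned power optimistic. The secondary outcomes would inherit the problem. So would the Economic evaluation, which uses statistical significance to decide which outcomes receive a cost-effectiveness or cost-utility analysis. Household co-allocation is a second source of dependence, in both arms, that the model also leaves out.

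**Working it through.** **Inputs from the Sample size section:** difference 2.1 mg, SD 5.3 mg, power 80%, significance level 5% (taken as two-sided, because that reproduces the stated figure), and two 20% allowances.

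**Reproducing the plan's figures**
- Normal approximation: n per arm = 2 × (5.3 × (1.960 + 0.842) / 2.1)² = 99.99, so 100.
- t-test version: 100.96, so 101 per arm, or 202. This matches.
- Recruitment: 101 / (1 − 0.40) = 168.3, so 169 per arm, or 338. This matches, so the two 20% allowances were added together. Applied in sequence they would give 202 / 0.64 = 316.

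Both figures are reached with nothing left over for clustering.

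**Assumptions, because the article gives neither figure:** m = 5 to 10 analysed per course and ICC = 0.01 to 0.10. All analysed intervention participants are taken to be clustered and controls independent. Household dependence is left out, because the number of shared households is not given.

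**Formulas**
- Intervention-arm design effect: DE = 1 + (m − 1) × ICC
- Variance of the difference relative to independence: R = (1 + DE) / 2
- Independence standard error at 101 per arm: 5.3 × √(2/101) = 0.746; true standard error = 0.746 × √R
- Power = Φ(2.1 / (0.746 × √R) − 1.96)
- True error of the nominal 5% test = 2 × (1 − Φ(1.96 / √R)), for course effects that average zero

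**Example, m = 8 and ICC 0.05:** DE = 1 + 7 × 0.05 = 1.35. R = 2.35 / 2 = 1.175 and √R = 1.084. The true standard error is 0.81. Power = Φ(2.598 − 1.96) = 73.8%. True error = 2 × (1 − Φ(1.808)) = 7.1%.

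| m | ICC | DE | R | Power at 101 per arm | True error |
|---|---|---|---|---|---|
| none | 0 | 1.00 | 1.000 | 80.4% | 5.0% |
| 5 | 0.01 | 1.04 | 1.020 | 79.6% | 5.2% |
| 5 | 0.10 | 1.40 | 1.200 | 72.9% | 7.4% |
| 8 | 0.05 | 1.35 | 1.175 | 73.8% | 7.1% |
| 10 | 0.05 | 1.45 | 1.225 | 72.0% | 7.7% |
| 10 | 0.10 | 1.90 | 1.450 | 64.7% | 10.4% |

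The table uses the normal approximation, so its starting point is 80.4%; the t-test gives 80.0%.

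**Effect of non-attenders.** A person who never joins a course is not clustered but stays in the complete-case analysis if the accelerometer data are valid. Suppose, for illustration, that 20% of the analysed intervention arm never joins. At m = 8 and ICC 0.05 the average design effect is 0.8 × 1.35 + 0.2 × 1 = 1.28, so R = 1.14, power is about 75.1% and true error about 6.6%. The table is therefore an upper bound on the problem if non-attenders are analysed.

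**The case against.** **The ICC may be small.** The outcome is each person's own accelerometry at 12 months, adjusted for baseline. The four sessions are about two weeks apart and start within about a month of consent, so group contact ends some 9 months before the outcome. Later support is automated text messaging, and individual goal setting is a key part of the programme. This stands: it makes the upper end of the ICC range less likely, and at the low end the loss is under one point of power.

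**A reader might infer that the type I error definitely exceeds 5%.** The document does not support that. With individual randomisation, and households aside, if the programme affects nobody then shared locality or group composition does not inflate the test. Inflation needs real course-specific effects that happen to average zero.

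**A reader might infer that the trial must recruit more.** At m = 10 and ICC 0.05, restoring 80% power would take 246 evaluable, or 410 recruited at the same 40% allowance. Those inputs are assumed, so that figure is not a requirement. Nor would a cluster-trial design effect in both arms be right, since controls are ungrouped.

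**The 40% allowance may absorb the loss.** If only the 20% loss to follow-up removes data, about 135 per arm remain (169 × 0.8). Power is then about 90% under independence and about 84% at m = 10 and ICC 0.05. This ignores the dilution from non-attendance that the second 20% was meant to cover, and it does nothing for the standard error.

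**The analysis plan may deal with it.** The article defers to a detailed plan, and clustered standard errors would still be a linear regression with the same terms. That is fair as to the variance estimator. It does not reach the sample size, and the article has already set out the primary model without any allowance for course or household.

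**Conclusion.** The point holds in conditional form. It is certain that delivery is grouped in one arm, that households share an allocation, and that neither the power calculation nor the stated primary model allows for either. The consequence follows only if the within-course ICC is positive. The standard error is then too small and 80% power is overstated. On the assumed ranges the effect runs from negligible (79.6% power, 5.2% error) to material (64.7%, 10.4%), with every intervention participant treated as clustered. The example at 8 per course and ICC 0.05 illustrates the middle of those ranges and is not an estimate from the document. Confidence is high on the omission and low on its size. It should be corrected, but it does not by itself undermine the trial.

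**What to change.** - Record for each intervention participant the course they were allocated to or booked on. Treat those never booked, and all controls, as singletons, or as household clusters where a household is shared.
- Fit the primary model with a random course effect in the intervention arm only, using Satterthwaite or Kenward-Roger degrees of freedom. Alternatively, keep the linear regression and use standard errors clustered on course with a small-sample correction. The correction matters because 101 analysed in courses of 5 to 10 means only about 10 to 20 courses. Account for shared households in either version, and carry the approach to the secondary outcomes.
- Report the estimated ICC.
- Restate the power in the Sample size section over an assumed range of course size and ICC. This makes the stated power honest but does not restore it; recruitment need not increase.

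The cost is some wording in the analysis plan and one variable, which the team should already hold because it confirms venue and dates to each intervention participant by letter. The downside is slightly wider confidence intervals (about 8% wider at 8 per course and ICC 0.05, from √1.175 = 1.084) and a less favourable stated power. If the ICC proves near zero, little precision is lost.
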